## Methods

### Overview

Once reviewed by the Imperial College Research Ethics Committee, we will recruit 30 healthy older adults (aged 65-90 years) in 3 cohorts through the UK DRI CRT community outreach group community outreach in West London. Participants will have access to the conversational agent through WhatsApp chat. We estimate that the average conversation will take less than 10 minutes. Each participant will also have access to the Withings sleep analyzer provided by the research group.

A poststudy questionnaire consisting of the GPIS, TPS, and NPS will be completed when the participant finishes the study. We analyze participants’ answers to assess the participants’ opinions on the proposed MotivSleep chatbot’s intelligence, trustfulness, and participants’ satisfaction with MotivSleep, to answer RQ1. Additionally, all participants will complete the ESS, ISI, modified PSQI, and SQS questionnaires before the start, fortnightly during the study, and at the end of the study. We analyze the answers to these questions to investigate RQ2.

The first cohort of 10 participants will use both the Withings sleep analyzer for 6 weeks (the first 2 weeks aims to establish baseline sleep assessments without the usage of MotivSleep) and the WhatsApp chatbot for 4 weeks, with WhatsApp message reminders to encourage WhatsApp chatbot engagement sent out fortnightly (ie, twice for the first cohort of 10 participants). The first batch of participants’ feedback and engagement measures will inform a new iteration of improvements.

The second cohort of 10 participants and the third cohort of 10 participants will use the WhatsApp chatbot for 8 weeks and 12 weeks and the Withings sleep analyzer for 10 weeks and 14 weeks, respectively. Participants will be reminded fortnightly (ie, 4 times for the second cohort participants and 6 times for the third cohort participants) to encourage participation with the WhatsApp chatbot when activated. After each cohort, participants’ technical feedback will be addressed by improving the software.

The feasibility study will have a single experiment condition that includes three types of features:

A sleep tracking device (ie, Withings sleep analyzer) and sleep analysis model.A chatbot (ie, MotivSleep) hosted on WhatsApp that conducts sleep interviews. The dialogue is designed to understand the reason behind participants’ sleep problems, provide personalized recommendations for better sleep, and support behavior changes to improve their sleep assessments.WhatsApp messages that encourage interaction with MotivSleep.

We will measure three classes of outcome variables as follows:

Assess the feasibility and usability of our proposed chatbot MotivSleep (RQ1)—the number of interactions in each MotivSleep conversation and time spent chatting with MotivSleep, and the poststudy questionnaire consisting of NPS, GPIS, and TPS.Assess the subjectively perceived sleep assessments (before, during, and after the study) (RQ2)—ESS, ISI, PSQI, and SQS questionnaires.Assess the objectively measured sleep assessments (before, during, and after the study) (RQ3)—obtained from the Withings sleep analyzer and analyze using the Withings provided sleep analysis models.

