**Methods:**

We will recruit 30 older adult participants from West London for this pilot study. Each participant will have a sleep analyzer installed under their mattress. This contactless sleep monitoring device passively records movements, heart rate, and breathing rate while participants are in bed. In addition, each participant will use our proposed chatbot MotivSleep, accessible on WhatsApp, to describe their sleep and behaviors related to their sleep and receive personalized recommendations for better sleep tailored to their specific reasons for disrupted sleep. We will analyze questionnaire responses before and after the study to assess their perception of our proposed chatbot; questionnaire responses before, during, and after the study to assess their subjective sleep quality changes; and sleep parameters recorded by the sleep analyzer throughout the study to assess their objective sleep quality changes.

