### Research Questions

The MotivSleep chatbot used in this feasibility study has been co-designed with patients, carers, and other health professionals. Together, we identified the following research questions:

*RQ1* Is our proposed MotivSleep chatbot accessible to participants, and how feasible is it to engage the participants with interviews using MotivSleep? We focus on assessing the feasibility and usability of our proposed MotivSleep, by measuring the number of turns and time spent chatting with the skill per engagement. Moreover, we assess MotivSleep’s accessibility by asking participants to rate their willingness to promote the chatbot using the net promoter score (NPS) [31] question in the exit questionnaire. Finally, we assess the participants’ perception of the chatbot by asking participants to complete the Godspeed Perceived Intelligence subscale (GPIS) [32] and Trust Perception Scale-Human Robot Interactions (TPS) [33] questionnaires.*RQ2* Can our proposed MotivSleep chatbot help improve participants’ subjective sleep assessment? We aim to evaluate the participants’ self-reported sleep assessment to analyze if the proposed MotivSleep helps participants to subjectively sleep better through the completion of the Epworth sleepiness scale (ESS) [34], Insomnia Severity Index (ISI) [35], modified Pittsburgh sleep quality index (PSQI) [36], and the single-item sleep quality scale (SQS) [37], conducted at the beginning, the end, and every 2 weeks throughout the study.*RQ3* Can our proposed MotivSleep chatbot help improve participants’ sleep, measured using the Withings sleep analyzer? We aim to analyze participants’ objective sleep assessments using sleep recordings gathered by Withing sleep analyzer throughout the study.

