### Recruitment

This study will be conducted in 3 batches. Participants in all 3 batches will be healthy older adults with no neurodegenerative disease. The participants will be recruited through the UK DRI CRT community outreach group in West London. The recruitment process follows the recommendations and requirements laid out in the UK National Institute for Health and Care Research Clinical Research Network policy, based on the inclusion and exclusion criteria. Specifically, Participants should be aged between 65 and 90 years, able to communicate fluently in English, experiencing sleep problems and wanting to improve their sleep, willing to install a Withings sleep analyzer and use the WhatsApp chatbot and have access to high-speed wireless internet connection at home, and able to provide informed consent. The exclusion criteria include the following: (1) people with unstable mental states, including severe depression, severe psychosis, agitation, and anxiety; (2) people with severe sensory impairment; (3) people who have active suicidal thoughts; (4) people who are receiving treatment for terminal illnesses.

Participants will be compensated for their time and inconvenience with £25 (US $31.15) per 2 weeks for participation, that is, for filling out the prestudy informed consent and questionnaires before, during, and after the study and engaging with the chatbot. The questionnaires will be provided on Qualtrics, separately to the chatbot, and sent to the participants as WhatsApp messages. Additionally, our team will teach the participants to complete the questionnaire using their smartphones before the study on an in-person visit when they sign the consent form. The subsequent questionnaires during the study will be sent to their mobile as WhatsApp messages.

A total of 30 individuals will be recruited in 3 cohorts. In total, we aim to include 18% of individuals who self-identify as members of a minority ethnic group to ensure alignment with the UK population [38] and avoid exclusion. Only approved phone numbers (of people who have consented to the study) can interact with the chatbot.

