## Results

The planning and development of this study started in August 2022. We have since developed the chatbot MotivSleep. The chatbot’s design is being evaluated by carers, health care professionals, and occupational therapists and will be updated after their evaluation. The first cohort of participation recruitment will start in May 2023, the second cohort will begin in June 2023, and the third cohort will start in August 2023. The anticipated study completion date is December 2023.

In this study, we aim to test three hypotheses as follows:

First, we hypothesize that participants will perceive our chatbot as intelligent and trustworthy and are satisfied with our proposed MotivSleep.We also hypothesize that our proposed chatbot MotivSleep can improve participants’ subjective sleep assessment over their usage of the chatbot based on collected using ESS, ISI, PSQI, and SQS questionnaires and their objective sleep quality based on the Withing sleep analyzer.Finally, we hypothesize that participants’ objective sleep assessment will improve, measured by the Withings sleep analyzer.

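### Chatbot perception is rated once, at the end of the study: the abstract states a different timing, and the single rating puts hypothesis 1 at risk of resting on completers

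*Protocol article*

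**What the plan says.** The protocol article gives the timing of the perception scales (GPIS, TPS, NPS) in four places.

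- **Abstract, Methods:** "We will analyze questionnaire responses before and after the study to assess their perception of our proposed chatbot".
- **Research Questions, RQ1:** participants will "rate their willingness to promote the chatbot using the net promoter score (NPS) [31] question in the exit questionnaire". GPIS and TPS are named with no time point.
- **Methods, Overview:** "A poststudy questionnaire consisting of the GPIS, TPS, and NPS will be completed when the participant finishes the study".
- **Methods, Overview, outcome list for RQ1:** conversation counts and time spent chatting, "and the poststudy questionnaire consisting of NPS, GPIS, and TPS".

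The first hypothesis, in the Results section, depends on these scales: "we hypothesize that participants will perceive our chatbot as intelligent and trustworthy and are satisfied with our proposed MotivSleep". On sample size, Recruitment says: "A total of 30 individuals will be recruited in 3 cohorts". The Overview puts 10 people in each cohort, gives chatbot use of 4, 8 and 12 weeks in turn, and says that the software is improved after each cohort.

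The sleep questionnaires are handled differently. ESS, ISI, modified PSQI and SQS are completed by everyone at the start, every two weeks and at the end.

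**The concern.** There are two issues, and neither causes the other.

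**Timing.** The abstract implies a perception measurement before the study. Nowhere does the body describe one, and a rating of a chatbot's intelligence or of trust in it has little meaning before the person has used it. A reader of the abstract alone would expect data that the described schedule does not produce.

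**Who is rated, and when.** With one scheduled rating at the end, a person who gives up in week 3 of a planned 12 may leave no opinion of the chatbot, although that person would already have returned at least one fortnightly sleep questionnaire. In a feasibility study, the views of people who abandon the tool matter a great deal. The planned period in which someone can leave before the rating is three times as long in cohort 3 as in cohort 1 (12 against 4 weeks). Because the software also changes between cohorts, a better score in a later cohort could reflect improved software, longer use, or greater loss of dissatisfied users. End-only ratings cannot separate these, and no later analysis can recover a rating that was never requested.

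**Working it through.** **Step 1. The timing statements side by side.**

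| Place | Timing of perception scales |
|---|---|
| Abstract, Methods | before and after |
| Research Questions | NPS in an exit questionnaire |
| Methods, Overview (text) | once, on finishing |
| Methods, Overview (outcome list) | poststudy |

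The three statements in the body agree with one another, and the abstract differs from them. The body does give repeated timing for the sleep scales (Research Questions, Overview, Analysis Plan) but never for GPIS, TPS or NPS. This suggests that the abstract's phrase is the one out of line.

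**Step 2. Possible size of a completer-only result.** The article gives no dropout rate, expected score or standard deviation, so there is no figure of its own to reproduce. Apart from the 30 enrolled, every input below is an assumption.

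Let f be the share who leave before rating.

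NPS of all enrolled = (1 - f) × NPS of completers + f × NPS of leavers

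Assume a completer NPS of +30. This is the value that would be reported in every row if only completers answered.

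| Leavers of 30 | f | Leavers' NPS 0 | All leavers detractors (NPS -100) |
|---|---|---|---|
| 0 | 0.0 | +30 | +30 |
| 3 | 0.1 | 0.9 × 30 = +27 | 27 - 10 = +17 |
| 6 | 0.2 | 0.8 × 30 = +24 | 24 - 20 = +4 |
| 9 | 0.3 | 0.7 × 30 = +21 | 21 - 30 = -9 |

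For a mean score such as GPIS or TPS:

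Excess of the completer mean = f × (completer mean - leaver mean)

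With leavers 0.5 points lower, the excess is 0.05, 0.10 and 0.15 points for 3, 6 and 9 leavers. With leavers 1.0 point lower, it is 0.10, 0.20 and 0.30 points.

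**Step 3. Limits of the illustration.** The excess is zero if nobody leaves or if leavers rate the chatbot as completers do. It changes sign if leavers rate it higher. The last column of the NPS table is the extreme case. With 30 people, each missing rating is 1/30, or about 3.3%, of the sample, and within a cohort of 10 it is 10%.

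**The case against.** The strongest reply is that the article never says early leavers go unasked. The term exit questionnaire could mean one given whenever a person leaves. The article is a condensed account, and withdrawal procedures, analysis sets and missing-data handling are commonly left to the full protocol or SAP. This stands: a reader might infer that leavers are excluded, but the text does not settle the question. The wording about finishing the study points towards completion without proving it.

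Second, a reader might infer that perception is overstated as a matter of fact. The documents do not support that. It would require both that some people leave and that those who leave rate the chatbot lower, and the article gives a figure for neither. Participants want to improve their sleep, are willing to use the chatbot, and are paid £25 per two weeks, so heavy dropout cannot be presumed. Only a risk of upward bias can be claimed.

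Third, a reader might take the abstract to promise a change score for perception that cannot be computed. It does not. It speaks of change only for subjective and objective sleep, and no objective or hypothesis concerns a change in perception. The conflict is confined to stated timing.

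Fourth, RQ1 also uses the number of turns and time per conversation, which accrue during use and so exist for people who later stop. This is correct and softens the point for feasibility overall. It does not supply ratings of intelligence, trust or satisfaction, on which hypothesis 1 depends.

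Finally, week 4 is already the end of chatbot use for cohort 1, so an extra rating adds nothing there, and it misses those who leave sooner. Both are true, which is why the withdrawal trigger is needed as well. The gain from week 4 is a rating at equal exposure in all three cohorts.

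**Conclusion.** The two points hold, with different certainty.

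1. The mismatch between the abstract and the body is plain on the page. It is a matter of wording and biases nothing.
2. The single end-of-study rating exposes hypothesis 1 to selection towards completers, probably in a favourable direction, and mixes length of exposure with software changes when cohorts are compared. The size is unknown. Under the assumed completer NPS of +30 and 3 to 9 leavers of 30, the overstatement would run from 3 to 9 points if leavers score 0, and from 13 to 39 points if all are detractors. It would be zero with no leavers or with equal ratings.

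The change is worth making because the collection schedule is fixed here and cannot be repaired at analysis. If the sponsor already surveys people who withdraw, one sentence saying so would remove most of the selection concern, though unequal exposure at rating would remain.

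**What to change.** - Reconcile the timing, for example by correcting the abstract to say that perception is measured only after exposure to the chatbot.
- State that anyone who stops early is sent the same Qualtrics questionnaire (GPIS, TPS, NPS) at withdrawal.
- Add one rating at week 4 of chatbot use in cohorts 2 and 3. In cohort 1 this is the existing end-of-study rating. Week 4 then allows cohorts to be compared at equal exposure, and the end rating in cohorts 2 and 3 shows what longer use adds.
- Report how many of the 30 answered, by cohort, with a sensitivity analysis that gives non-responders the worst rating (detractor for NPS, lowest score for GPIS and TPS).

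The cost is small. The questionnaires already run on Qualtrics and are sent through WhatsApp, so this needs extra triggers for an existing link and a few sentences of text. Leavers and cohorts 2 and 3 spend a few more minutes, and the reported scores may be less favourable.

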### Recruitment

This study will be conducted in 3 batches. Participants in all 3 batches will be healthy older adults with no neurodegenerative disease. The participants will be recruited through the UK DRI CRT community outreach group in West London. The recruitment process follows the recommendations and requirements laid out in the UK National Institute for Health and Care Research Clinical Research Network policy, based on the inclusion and exclusion criteria. Specifically, Participants should be aged between 65 and 90 years, able to communicate fluently in English, experiencing sleep problems and wanting to improve their sleep, willing to install a Withings sleep analyzer and use the WhatsApp chatbot and have access to high-speed wireless internet connection at home, and able to provide informed consent. The exclusion criteria include the following: (1) people with unstable mental states, including severe depression, severe psychosis, agitation, and anxiety; (2) people with severe sensory impairment; (3) people who have active suicidal thoughts; (4) people who are receiving treatment for terminal illnesses.

Participants will be compensated for their time and inconvenience with £25 (US $31.15) per 2 weeks for participation, that is, for filling out the prestudy informed consent and questionnaires before, during, and after the study and engaging with the chatbot. The questionnaires will be provided on Qualtrics, separately to the chatbot, and sent to the participants as WhatsApp messages. Additionally, our team will teach the participants to complete the questionnaire using their smartphones before the study on an in-person visit when they sign the consent form. The subsequent questionnaires during the study will be sent to their mobile as WhatsApp messages.

A total of 30 individuals will be recruited in 3 cohorts. In total, we aim to include 18% of individuals who self-identify as members of a minority ethnic group to ensure alignment with the UK population [38] and avoid exclusion. Only approved phone numbers (of people who have consented to the study) can interact with the chatbot.

### Data Management

WhatsApp messages are automatically encrypted, so conversations are private and cannot be accessed by Meta (the mother company of WhatsApp).

We will create 2 databases in Microsoft Azure, where both databases are only accessible through designated virtue private network connections, which are available only to the app and the researchers. We will use the Research Data Storage (RDS) managed by the Imperial College London to host the data sets after obtaining them through Azure. RDS is only available to researchers within the project through university-hosted Virtual Private Network connections.

Specifically, we will first pseudoanonymize each user by assigning them an automatically generated user ID and storing this information in a secure Azure database. MotivSleep then automatically stores the transcripts anonymously in a second secure database. Both databases are hosted on Azure before being transferred to RDS. After moving both user information and transcripts to RDS, they will be permanently deleted from the Azure databases. There will be 2 copies of sleep tracking data, that is, Withings will store 1 copy, and the RDS will store another copy. Responses to the questionnaires will be stored in Qualtrics servers.

According to the Imperial College data retention policy, the data will be retained for at least 12 years.

### Analysis Plan

We aim to analyze the following four types of data:

The dialogue transcripts: dialogue transcripts can help us understand how much time participants spend talking to the chatbot, what sleep behaviors each participant exhibits, and how often these behaviors appear when troublesome sleep patterns are detected.The answers to the GPIS and TPS questionnaires: these answers help us to understand how participants perceive our proposed chatbot MotivSleep, in terms of usability, feasibility, intelligence, and trustfulness.The answers to the ESS, ISI, modified PSQI, and SQS questionnaires before, during, and after the study help us analyze participants’ subjective views of their sleep assessments and provide insights into their perceived sleep changes over time.The sleep data tracked by the sleep tracking device Withings sleep analyzer: Sleep tracking helps us monitor participants’ objective sleep assessment changes over time, measured by the tracking devices unrelated to participants’ subjective feeling of their sleep.

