**Objective:**

This work aims to (1) determine the feasibility and usability of an automated chatbot (named MotivSleep) that conducts sleep interviews to encourage the aging population to report behaviors that may affect their sleep, followed by providing personalized recommendations for better sleep based on participants’ self-reported behaviors; (2) assess the self-reported sleep assessment changes before, during, and after using our automated sleep disturbance intervention chatbot; (3) assess the changes in objective sleep assessment recorded by a sleep tracking device before, during, and after using the automated chatbot MotivSleep.

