The objective sleep assessment: sleep quality is highly challenging to assess, with a range of potential models for data fusion from the internet of things devices. In the context of our study, we will initiate analyses of the objective sleep assessment using measures provided by the installed Withings sleep analyzer. Specifically, MotivSleep starts at a predefined time each day and calculates the sleep quality using the sleep tracking device. If the triage result is red or yellow, MotivSleep will continue to the next stage to start the chatbot and engage with the participant; otherwise, MotivSleep will not send the initial text message and will quit automatically. We note that the UK DRI CRT has ongoing work in sleep quality evaluation using the Withings sleep analyzer, which could be incorporated into the study for comparison when available.The subjective sleep assessment: MotivSleep chatbot activates the interview through WhatsApp and asks the participant, “Did you sleep well last night?” This stage helps MotivSleep confirm with the participant if they had a bad night’s sleep. If the participant denies having had a bad sleep, our chatbot will go to stage 7, wishing them a good day and quitting. However, if the participant confirms that they have had a bad night, the chatbot will continue to ask the next question.Redocumentation of consent: the chatbot will briefly remind the participant about the study, ask them for their consent to participate in the current interactions, and provide insights into their poor sleep. If they do not consent, the chatbot will go to stage 7, where we thank them for their engagement, and the chat ends; otherwise, the chatbot will continue to the next stage.The information-seeking stage: in this stage, the chatbot will ask the participant for reasons that might explain why they did not sleep well the previous night. This open question seeks insights into participant’s behaviors before and during their sleep that may have contributed to a bad night’s sleep. Answers to this question are collected and analyzed, and the analysis result will prompt the following three types of further questions:In-depth questions related to predefined specific reasons that cause their poor sleep. These questions will be triggered if we identify predefined reasons from the participant’s answers;Multiple-choice questions consist of potential reasons that might cause poor sleep. These questions will be asked if the participant answers that they do not know why they had a poor sleep;Similar questions to the previously asked question (ie, why did you sleep poorly?) until they confirm there is no more information to add. These questions will be asked if the reasons the participant provided early are not one of the predefined reasons.Agreement to receive personalized recommendations for better sleep: in this stage, the chatbot will ask the participant whether they want to hear personalized recommendations for better sleep. If they disagree, the chatbot will go to stage 7, where we thank them for their engagement, and the chat ends; otherwise, the chatbot will continue to the next stage.Provide personalized recommendations for better sleep: in this stage, we provide specific recommendations to the participant based on the information gathered during stage 4. Furthermore, we provide a motivational summary of what was covered today, including their reasons for poor sleep and recommendations for better sleep.The end of the conversation: in this stage, we thank the participant for the engagement, wish them a good day, and end the conversation. To further motivate the participants, the chatbot also praises the participant if some of the repeated behaviors negatively affecting their sleep were not mentioned in this interaction.

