## Discussion

### Principal Findings

Sleep disturbances are commonly observed among older people, with and without neurodegenerative disorders, and among carers for people with neurodegenerative disorders. This study will provide critical evidence pertaining to the feasibility and acceptability of the proposed chatbot MotivSleep, hosted on WhatsApp, which aims to conduct automatic sleep interviews and provide personalized recommendations for better sleep that may improve their sleep. Specifically, we evaluate the participants’ perceived usability and feasibility of the chatbot, changes in participants’ subjective sleep assessment before, during, and after the study, and changes in participants’ objective sleep assessment measured by the sleep tracking device Withings sleep analyzer.

This paper describes the protocol used in the MotivSleep study. To the best of our knowledge, no other studies have focused on developing an automated chatbot for older people with problematic sleep or conducting automated sleep interviews. The MotivSleep study aims to shed light on the feasibility of using a chatbot to conduct interviews for a prolonged period of time. Furthermore, the intervention and protocol were designed to be more accessible and simpler than frequent in-person assessment or intervention sessions. This allows future deployment to older adults with mobility issues or within hard-to-reach communities.

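### Objective 1 promises usability, but none of the five listed measures is named as a direct usability measure, so any usability conclusion would rest on indirect proxies

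*Protocol article*

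**What the plan says.** Objective 1 in the Abstract pairs feasibility with usability. Principal Findings in the Discussion returns to it: "we evaluate the participants’ perceived usability and feasibility of the chatbot".

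The measures are assigned in four places:

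- Research Questions, RQ1: "We focus on assessing the feasibility and usability of our proposed MotivSleep, by measuring the number of turns and time spent chatting". The NPS is there for accessibility, and GPIS and TPS are there for perception of the chatbot.
- Methods, Overview, on the exit questionnaire: GPIS, TPS and NPS are to give participants' opinions on intelligence, trustfulness and satisfaction.
- Methods, Overview, list of outcome classes: interactions, time, NPS, GPIS and TPS all stand together under feasibility and usability.
- Analysis Plan: the GPIS and TPS answers show "how participants perceive our proposed chatbot MotivSleep, in terms of usability, feasibility, intelligence, and trustfulness". The NPS is not mentioned.

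The matching hypothesis under Results covers intelligence, trustworthiness and satisfaction. It does not mention usability.

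Chatbot Features sets out what governs the length of a chat. The conversation ends early if the participant reports having slept well, does not consent to that day's interaction, or declines recommendations. At stage 4 there are three kinds of follow-up: in-depth questions, multiple-choice questions, or repeats of the open question. On the repeats: "These questions will be asked if the reasons the participant provided early are not one of the predefined reasons".

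**The concern.** Usability is half of the first objective, and the participants are aged 65 to 90. Whether they can operate the chatbot without difficulty is something this study should be able to report directly.

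The two places that say where usability will be read from do not agree, and neither is convincing. The Analysis Plan takes it from two scales that, by the names the protocol gives them, concern perceived intelligence and trust. RQ1 takes it from turns and time, which describe how much conversation took place and not how easily it went. If this stands, the report could draw a usability conclusion from scores on other constructs, and two readers could reach opposite conclusions from the same turn counts.

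This is not a detail left to an unseen analysis plan. The article names its instruments one by one and states what each is for; the difficulty lies in those statements.

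**Working it through.** No arithmetic applies: the plan gives no target or criterion for usability. The check is to set the stated purposes side by side.

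| Measure | RQ1 | Methods, exit questionnaire | Methods, outcome list | Analysis Plan |
|---|---|---|---|---|
| Turns | feasibility, usability | – | feasibility, usability | not mentioned |
| Time | feasibility, usability | – | feasibility, usability | read from transcripts; no link to usability stated |
| NPS | accessibility | satisfaction | feasibility, usability | not mentioned |
| GPIS | perception | intelligence | feasibility, usability | usability, feasibility, intelligence, trust (jointly with TPS) |
| TPS | perception | trust | feasibility, usability | as GPIS |

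The Methods paragraph names three instruments and three constructs without pairing them; the pairing in the third column follows the instruments' names.

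Three things follow.

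1. *Direct measures.* Of the five, none is introduced as a usability scale, an ease-of-use item, a task-completion measure or an error measure. The count is 0 of 5.

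2. *Consistency.* No questionnaire keeps one meaning throughout. The NPS stands for accessibility, satisfaction, or feasibility and usability, depending on the section. GPIS and TPS acquire usability in the outcome list and the Analysis Plan, but not in RQ1 or the exit-questionnaire paragraph.

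3. *Direction of turns and time.* No section says whether more or fewer turns, or more or less time, counts as more usable. The Methods overview expects an average chat of under 10 minutes, but as an estimate and not as a criterion. Going through the dialogue rules:
   - A short chat may mean that the participant slept well, declined consent that day or did not want recommendations. It may also mean that they gave up.
   - A long chat may mean that a recognised reason led to in-depth questions, that an uncertain participant was taken through multiple-choice questions, or that a reason outside the predefined list led to repeated open questions. It may also mean slow or laboured use.

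   Length therefore mixes last night's sleep, the participant's reason and the participant's ease with the tool. The plan does not say how to separate them.

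**The case against.** The strongest reply is that this is a small feasibility study, and that turns, time and willingness to recommend do carry some information about use and acceptance. The Methods overview also collects participants' feedback after each cohort and uses it to improve the software, which is where operating difficulties would be expected to surface. That stands. It is why the evidence should be called indirect and not absent. The feedback is not listed as an outcome for Objective 1, however, so it does not fill the gap in the measures.

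A reader might infer several stronger things that the protocol does not support:

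- *That usability cannot be answered at all.* The proxies above give some evidence.
- *That the repeat-question branch is a failure of the tool that inflates turns.* All three stage 4 branches add turns, and the protocol gives no branch lengths, so it cannot be said that an unlisted reason makes a longer chat than a recognised one. The branch ends when the participant has nothing to add and may be intended elicitation. Any percentage for extra turns would need an invented chat length.
- *That someone who struggles would still score well everywhere.* Such a person could give a low NPS or leave chats early.
- *That no questionnaire item touches ease of use.* The items are not reproduced. The names and stated purposes show only that the scales are not presented as usability measures.
- *That the software revisions would be steered by turns and time alone.* Participants' feedback also guides them.
- *That the sample of 30 is undermined.* Limitations cites usability and feasibility together, and nothing ties the number to a particular instrument.

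**Conclusion.** The point holds as a mismatch between a stated objective and its stated measures. Usability is promised in the objective and the Discussion, 0 of the 5 listed measures is named as measuring it directly, and the sections disagree on what the measures are for. A usability conclusion drawn from this plan would rest on proxies for engagement, willingness to recommend, perceived intelligence and trust.

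This rests on the protocol's own naming of the instruments and on its lists of measures being complete, as they are written. It does not rest on any assumption about chat length or item content. It does not affect the sleep objectives. It is worth correcting before the exit questionnaire is fixed, because a scale not given at exit cannot be recovered afterwards.

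**What to change.** 1. Add one short validated usability scale to the Qualtrics exit questionnaire and name it as the usability measure for Objective 1.
2. In the Analysis Plan, restrict GPIS to perceived intelligence and TPS to trust.
3. Give each of the five existing measures, including the NPS, one stated purpose, and use it consistently in RQ1, both places in the Methods overview and the Analysis Plan.
4. Report turns and time as engagement. They may also be described by dialogue branch from the stored transcripts. Do not label repeat-question chats as failures, and do not drop their turns.

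If no scale is added, remove usability from Objective 1, RQ1, the outcome list, the Analysis Plan and Principal Findings, or say in those places that the evidence on usability is indirect.

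The cost is about 10 extra items once per participant, or about 30 × 10 = 300 item responses over the whole study, plus edits to the text. The branch description needs no new data.
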